#### Depressive symptoms

The Patient Health Questionnaire-9 (PHQ-9) [12] measures depressive symptoms over the past two weeks with nine items rated from 0 (not at all) to 3 (nearly every day). Total scores range from 0 to 27 and can be categorized into minimal, mild, moderate, and severe depression. Reliability is high (Cronbach’s α = 0.89).

#### Anxiety symptoms

The Generalized Anxiety Disorder Scale-7 (GAD-7) [13] assesses anxiety symptom frequency over the past two weeks with seven items rated from 0 (not at all) to 3 (nearly every day). Internal consistency is excellent (Cronbach’s α = 0.92).

#### Substance use

Alcohol use is measured with the 3-item Alcohol Use Disorders Identification Test -Consumption (AUDIT-C) [14]. The AUDIT-C demonstrated excellent internal consistency (Cronbach’s α = 0.98) [15].

Drug use is screened with the 11-item Drug Use Disorders Identification Test (DUDIT). The DUDIT showed good to excellent internal consistency (Cronbach’s α = 0.80) [16].

Both are scored on 5-point Likert scales and are based on ICD-10 and DSM-5 diagnostic criteria.

#### Health literacy

Perceived health literacy is assessed with the European Health Literacy Survey Questionnaire (HLS-EU) [17]. Sixteen items measure how easy or difficult it is to access, understand, evaluate, and apply health-related information (1 = very easy, 4 = very difficult). The internal consistency is good (Cronbach’s α = 0.88) [18].

#### Psychosocial functioning

Broader functioning is measured with the Barkley Functional Impairment Scale (BFIS) [19]. This validated, norm-referenced self-report tool assesses impairment across 15 life domains. Each item is rated on a 10-point scale (0 = not at all, 8–9 = severe). The BFIS showed excellent internal consistency (Cronbach’s α = 0.97) [20].

#### Medication adherence

For participants currently using ADHD medication, adherence is assessed with the Medication Adherence Report Scale – German version (MARS-D) [21]. The five items are scored on a 5-point scale from never (5) to always (1). The MARS-D has satisfactory internal consistency (Cronbach’s α = 0.60–0.69).

### Additional measures and assessments

#### User satisfaction

Satisfaction with the digital intervention is measured at T2 using the Client Satisfaction Questionnaire-8 (CSQ-8) [22,23]. The eight items are rated on a 4-point scale, with higher total scores reflecting greater satisfaction. The CSQ-8 shows good psychometric properties (α = 0.88–0.92) [24].

#### Self-stigma

Internalized stigma is assessed with the 9-item short form of the Internalized Stigma of Mental Illness Scale (ISMI-9) [25]. Items are rated on a 4-point Likert scale (strongly disagree to strongly agree). The short form demonstrates strong reliability and validity comparable to the full version.

#### Intervention adherence

Engagement with the digital program is tracked descriptively using log-file data (frequency of access and number of completed modules).

### Statistical analyses

#### Sample size

The sample size was calculated in G*Power (version 3.1) [26] for an independent-samples *t*-test targeting the primary endpoint. Assuming a medium effect (Cohen’s *d* = 0.40), two-tailed α = 0.05, and 1−β (power) = 0.90, the required total sample is *N* = 266 (133 per group). Because digital interventions commonly face attrition around 25 % (e.g., [27]), we inflated the sample by 30 %. The resulting recruitment target is *N* = 380 (*n* = 190 per group). This calculation is conservative relative to the mixed-models approach planned for the primary analysis. All analyses will be performed using IBM SPSS^Ⓡ^ Statistics 31 and R 4.4.3 [28].

### Analysis populations

#### Complete cases (CC) analysis

The complete case analysis (CC analysis) includes all data sets from participants for whom both baseline and post-intervention data are available.

#### Intention-to-Treat (ITT) analysis

The intention-to-treat (ITT) analysis includes data sets from all randomized participants. The ITT analysis will be conducted as the primary analysis.

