## Description of protocol

### Overview

As illustrated in Fig. 1, the trial follows a two-arm randomized controlled design with three assessments. Participants are randomly assigned to either the intervention group (IG) or a care as usual group (CAU). Assessments take place at baseline prior to the intervention (T0), at 6 weeks (T1), and at 12 weeks (T2).

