### Recruitment

Recruitment will be conducted via the University Medical Center Hamburg-Eppendorf (UKE). In addition, further recruitment will take place through other sources including email contact with individuals who previously expressed interest in the pilot study (DRKS00033320), referrals by clinicians at the specialized ADHD outpatient clinic of the UKE, online advertisements (e.g., social media and patient organizations such as *ADHS Deutschland e.V.*), and self-initiated contact by interested individuals via a dedicated study email address. The planned recruitment period is three months. Individuals recruited online must submit written proof of their diagnosis before they can access the baseline survey. Participants may withdraw from the study at any time without providing a reason and without any negative consequences for their medical treatment or relationship with healthcare providers. Participation is voluntary and independent of routine care. Although recruitment occurs partly within healthcare settings, treating clinicians are not involved in obtaining consent, and refusal or withdrawal does not affect access to treatment as usual.

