#### Efficacy analyses

Primary efficacy will be evaluated at 12 weeks (T2), defined as the primary endpoint, using mixed models for repeated measures (MMRM), a likelihood-based approach suitable for longitudinal data and missingness under the missing-at-random assumption [29,30]. Models will include fixed effects for group, time, and group × time interaction, with baseline values entered as covariates. A random intercept for participants and an unstructured covariance matrix will be specified. Degrees of freedom will be estimated using the Kenward–Roger approximation.

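### The primary MMRM cannot use every randomized participant as the ITT definition says, and its missing-at-random assumption rests on too little baseline information

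*Protocol article*

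**What the plan says.** The section on the ITT analysis defines the set: "The intention-to-treat (ITT) analysis includes data sets from all randomized participants". It adds: "The ITT analysis will be conducted as the primary analysis".

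Efficacy analyses sets the T2 analysis as "using mixed models for repeated measures (MMRM), a likelihood-based approach suitable for longitudinal data and missingness under the missing-at-random assumption". On the model terms it says: "Models will include fixed effects for group, time, and group × time interaction, with baseline values entered as covariates". The Overview gives three assessments: T0, T1 at week 6 and T2 at week 12. Randomization and blinding places randomization after completion of baseline, so everyone randomized has T0 data. Table 2 lists the AAQoL, ASRS and PHQ-9 among the T0 assessments before randomization.

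Sensitivity analyses adds J2R analyses, labelled ITT, and complete-case analyses, both by ANCOVA. The Abstract likewise describes ITT as a complement to the MMRM. Both passages treat ITT as something beside the MMRM, whereas the ITT section makes it the primary analysis.

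Sample size expects attrition of about 25% and allows for 30%. It does not say how much of this falls before T1.

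**The concern.** Two statements do not fit together. If the primary analysis is ITT on everyone randomized, each of the 380 should be in it. A model with T0 as covariate and T1 and T2 as outcomes has no row for someone who answers neither follow-up. The headline result would then carry a label that does not describe the people behind it.

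The second issue is what missing at random is conditioned on. For a participant with no follow-up, the model knows only the arm and the baseline AAQoL. Allocation is open and controls wait for access, so the reasons for leaving before week 6 may differ between arms. If more severely depressed participants leave the app arm early and would also have had worse T2 quality of life than their baseline AAQoL predicts, those who remain in that arm are favourably selected. The contrast then leans towards the app.

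**Working it through.** **1. The plan's own figure.** A two-sample t-test with d = 0.40, two-sided alpha 0.05 and power 0.90 needs 132.3, so 133 per arm and 266 in total. Then 266 / (1 − 0.30) = 380. The sample size reproduces.

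**2. How many could be absent.** Attrition of 25% is 380 × 0.25 = 95, and 30% is 380 × 0.30 = 114. These are upper limits, reached only if all loss precedes T1. If 40–75% of it does (assumption), the range is 95 × 0.40 = 38 to 114 × 0.75 ≈ 86, or 10–23% of those randomized. With 133 per arm left, t-test power at d = 0.40 is still 0.90.

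**3. Does the absence itself move the contrast?** With a common baseline mean, the likelihood factors as f(T0) × f(T1, T2 | T0, arm). Participants with T0 only enter the first factor, which holds no treatment parameter. In one simulated trial of 380 with 51 such participants, the baseline-covariate MMRM gave a T2 effect of 0.493937 with or without them. A model with T0 in the outcome vector and all 380 also gave 0.493937. So the absence alone does not shift the estimate, and moving T0 to the outcome side does not change it either.

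**4. What omitting other baseline severity can do.** These inputs are assumptions, not in the article, in SD units:
- correlation of baseline AAQoL with T2: 0.5
- correlation of baseline AAQoL with PHQ-9: −0.5
- correlation of PHQ-9 with T2: r = −0.4 or −0.5
- all loss before T1: 20% at random in CAU; 28% or 30% in the IG, with log-odds rising by 0.4 or 1.0 per SD of PHQ-9

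Slope of T2 on PHQ-9 given baseline AAQoL: (r − 0.5 × (−0.5)) / (1 − 0.25) = (r + 0.25) / 0.75. This is −0.20 for r = −0.4 and −0.333 for r = −0.5.

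Mean PHQ-9 among IG stayers falls by 0.108 SD (log-odds 0.4, 28% lost) or 0.252 SD (log-odds 1.0, 30% lost), by numerical integration. Baseline AAQoL adjustment removes a quarter of this shift (0.5²) and leaves 0.75 of it.

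Bias ≈ shift × 0.75 × |slope|:
- smallest: 0.108 × 0.75 × 0.20 = 0.016
- largest: 0.252 × 0.75 × 0.333 = 0.063

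Simulation, 3,000 trials per cell, 190 per arm, true d = 0.40, ANCOVA at T2 on those observed. With all loss before T1, everyone with a follow-up has both visits, so this stands in for the MMRM's T2 contrast. Type I error comes from the same settings with d = 0; its Monte Carlo SE is about 0.004.

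| r | log-odds | Estimate (SE), AAQoL only | Estimate (SE), plus PHQ-9 | Type I error, AAQoL only | Type I error, plus PHQ-9 |
|---|---|---|---|---|---|
| −0.4 | 0.4 | 0.415 (0.102) | 0.398 (0.101) | 0.044 | 0.043 |
| −0.4 | 1.0 | 0.443 (0.103) | 0.405 (0.102) | 0.063 | 0.047 |
| −0.5 | 0.4 | 0.426 (0.102) | 0.398 (0.097) | 0.058 | 0.049 |
| −0.5 | 1.0 | 0.464 (0.103) | 0.401 (0.098) | 0.096 | 0.047 |
| −0.25 | 1.0 | 0.399 (0.103) | 0.399 (0.104) | 0.048 | 0.049 |

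The last row is the case where PHQ-9 adds nothing beyond baseline AAQoL: there is no bias, and the extra covariate does no harm. Independent runs of the first four settings gave estimates of 0.416 to 0.468 without PHQ-9, hence a bias of about +0.02 to +0.07.

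**5. If part of the loss comes after T1.** With 40–75% of loss before T1, later leavers contributing T1, and assumed correlations of 0.7 (T1–T2) and 0.55 (T0–T1), the bias is about +0.01 to +0.05.

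**The case against.** The strongest reply is that this is a labelling matter. The T1/T2 MMRM gives valid likelihood inference under the assumption the article states, and step 3 shows that participants without follow-up carry no information on the contrast. That stands. A reader might infer that leaving them out biases the result, or that no valid primary model exists. The documents support neither. A reader might also infer that putting T0 in the outcome vector cures the problem. It would bring the count to 380 in name only.

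It is also fair that the bias in step 4 comes from a predictor of dropout left out of the model, not from the analysis set, and that its inputs are assumed. The withdrawal wording under Recruitment is standard and is no evidence of early or differential loss. J2R, already planned, can cover every randomized participant and does not carry the app's benefit forward for IG leavers, so it works against the feared direction. Ranking it as a sensitivity analysis is a legitimate choice.

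Finally, covariate lists are often left to the SAP, which the article says is public but is not shown here. That excuses omissions. It does not reconcile two statements in the article that disagree about who is in the primary analysis. The phrase "with baseline values entered as covariates" names no variables; I read it as the baseline of the outcome being modelled, as in the planned ANCOVA. If it was meant to include other baseline measures, saying so would settle the second half of the point.

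**Conclusion.** The inconsistency is established from the text: the primary set is all randomized, while the primary model draws only on those with T1 or T2. Its direct effect on the contrast is nil under missing at random, and power is not at issue.

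The further weakness is conditional. Bias arises only if early loss differs by arm and depends on baseline severity that predicts T2 beyond baseline AAQoL. Under the assumptions in step 4 it is about +0.02 to +0.07 in d, or 0.2 to 0.7 of a standard error (0.07 / 0.102 ≈ 0.7). In the strongest case two-sided type I error rises to about 0.10. The bias is smaller if some loss follows T1, and absent if loss depends only on arm and baseline AAQoL with a common slope. The article gives neither the loss before T1 nor these correlations, so this is a plausible range, not a forecast. The change is worth making because it is cheap and did no harm in the case where the extra covariate was unnecessary.

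**What to change.** In Efficacy analyses, prespecify baseline PHQ-9 and baseline ASRS total as additional covariates in the primary AAQoL MMRM. Both are collected from everyone before randomization.

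In the ITT section, state that:
- the primary MMRM draws on randomized participants with at least one follow-up AAQoL;
- the J2R analysis covers all randomized participants;
- the number with no follow-up is reported by arm.

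Align the Abstract and Sensitivity analyses with this, so that it is clear how the MMRM and the ITT analyses relate.

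Cost: wording, a few lines of code and no new data. The model spends two extra degrees of freedom, the covariates must be fixed before data are seen, and the reported N of the primary model will fall below 380 if anyone has no follow-up.

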#### Descriptive analyses

Sociodemographic and clinical variables will be summarized using means and standard deviations for continuous variables and absolute frequencies and percentages for categorical variables.

#### Hypotheses

The primary hypothesis is that participants of the IG will show greater improvement in quality of life, as measured by the AAQoL, at 12 weeks (T2) compared to participants in CAU. Secondary hypotheses are that, at 12 weeks (T2), participants in the IG will demonstrate greater reductions in ADHD symptom severity (ASRS), global functional impairment (CGI-S), depressive symptoms (PHQ-9), anxiety symptoms (GAD-7), substance use (AUDIT-C, DUDIT), and greater improvements in health literacy (HLS-EU), daily functioning (BFIS), and medication adherence (MARS-D) compared to CAU.

#### Efficacy analyses

Primary efficacy will be evaluated at 12 weeks (T2), defined as the primary endpoint, using mixed models for repeated measures (MMRM), a likelihood-based approach suitable for longitudinal data and missingness under the missing-at-random assumption [29,30]. Models will include fixed effects for group, time, and group × time interaction, with baseline values entered as covariates. A random intercept for participants and an unstructured covariance matrix will be specified. Degrees of freedom will be estimated using the Kenward–Roger approximation.

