## Limitations

Some limitations should be considered. Participant blinding is not feasible due to the nature of the digital intervention and the waitlist control with CAU design, which may introduce expectancy effects. Outcomes are assessed exclusively via self-report, which may be subject to reporting bias. In addition, recruitment and adherence may be challenging, as digital interventions for ADHD can be associated with higher attrition rates. Although the waitlist design ensures that all participants eventually receive access to the intervention, it may raise ethical considerations related to delayed treatment for participants assigned to the control condition. This concern is mitigated by the relatively short waiting period, and the fact that participation does not restrict access to care as usual. Finally, the fully digital and self-guided format limits personal contact, which may affect engagement for some participants.

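### The primary MMRM as written has one baseline slope for weeks 6 and 12; a baseline × time term removes a possible small bias in the T2 contrast at almost no cost

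*Protocol article*

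**What the plan says.** The mean model of the primary analysis is given in one sentence of the Efficacy analyses section: "Models will include fixed effects for group, time, and group × time interaction, with baseline values entered as covariates". The next sentences fix the covariance ("A random intercept for participants and an unstructured covariance matrix will be specified") and the degrees-of-freedom method (Kenward–Roger). Time interacts with group only. Baseline appears solely in the words "with baseline values entered as covariates"; no interaction of time with baseline is listed.

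The same section sets the target, "Primary efficacy will be evaluated at 12 weeks (T2), defined as the primary endpoint", and justifies the method as "suitable for longitudinal data and missingness under the missing-at-random assumption". The Sample size section expects about 25 % attrition and inflates for 30 %. The Limitations section adds that "digital interventions for ADHD can be associated with higher attrition rates". The Specifications table says that a statistical analysis plan is public at the registry; it was not available for this review.

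**The concern.** With baseline as a covariate, the modelled visits are T1 and T2. A baseline main effect without baseline × time gives both visits the same slope. The unstructured covariance does not relax this, because it describes the residuals and not the regression on baseline.

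A likelihood analysis is valid under MAR only if the mean model is right. If baseline predicts week 12 less steeply than week 6, the shared slope is too steep at T2 and lost T2 values are implicitly predicted from it. When the participants who still have T2 data differ in baseline between the arms, that error does not cancel and enters the T2 contrast. AAQoL is the first step of the ten-step testing hierarchy, so the contrast that opens all the later tests is the one affected.

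**Working it through.** **Inputs from the protocol.** Effect d = 0.40, two-sided α = 0.05, power 0.90, 1:1 allocation, attrition about 25 % with 30 % used for inflation, post-baseline visits at weeks 6 and 12.

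**Inputs assumed.** The protocol gives no correlations between visits, no attrition by arm and no dropout mechanism. All of these are assumptions below, in baseline SD units with equal variances, so that slopes equal correlations.

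**Step 1: the plan's own figures.** The exact noncentral-t calculation gives 133 per arm (power 0.9015), total 266. Then 266 / 0.70 = 380. Both agree with the protocol.

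**Step 2: size of the bias by formula.** Let β₁ and β₂ be the true baseline slopes at T1 and T2, β_c the fitted common slope, γ the slope of T2 on T1 given baseline, and Δ the mean baseline of those with T2 data in the intervention group minus that in CAU. With T1 observed for all,

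bias ≈ k × Δ, where k = (β₂ − γβ₁) − β_c(1 − γ) and γ = (r₁₂ − β₁β₂) / (1 − β₁²).

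If β₁ = β₂ = β_c, then k = 0. If Δ = 0, the bias is also 0. Both conditions are therefore needed.

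Worked case, correlations T0–T1 0.7, T0–T2 0.5, T1–T2 0.7:
- γ = (0.70 − 0.35) / 0.51 = 0.686.
- The fitted common slope in the simulation below is 0.662, against a true T2 slope of 0.50.
- k = (0.50 − 0.686 × 0.70) − 0.662 × 0.314 = 0.020 − 0.208 = −0.188.
- Suppose that in the intervention group only, log-odds of dropout rise by 0.7 per SD of lower baseline, with 40 % lost there and 20 % in CAU. Integrating the logistic dropout model over a normal baseline gives Δ = 0.253.
- Bias ≈ −0.188 × 0.253 = −0.048.

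**Step 3: simulation.** A maximum-likelihood two-visit model with unstructured residual covariance was fitted to one run of 1,000,000 participants per scenario (true T2 effect 0.40). The formula result is in brackets; Δ = 0.383 for opposite directions.

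| Correlations T0–T1, T0–T2, T1–T2 | Same relation in both arms (baseline) | Intervention group only, 20/40 % lost | Opposite by arm, 30/30 % lost |
|---|---|---|---|
| 0.7, 0.7, 0.8 | −0.002 | −0.001 (0) | −0.002 (0) |
| 0.7, 0.6, 0.75 | −0.001 | −0.024 (−0.023) | −0.036 (−0.035) |
| 0.7, 0.5, 0.7 | 0.000 | −0.048 (−0.048) | −0.075 (−0.072) |
| 0.8, 0.4, 0.6 (extreme) | 0.000 | −0.098 (−0.099) | −0.150 (−0.151) |

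Complete data and completely random dropout also gave about zero. Dropout driven by T1 in the intervention group only gave −0.016, −0.034 and −0.078 in the last three rows. A milder case, with half the baseline imbalance and the second row's k of −0.091, gives 0.091 × 0.127 = 0.012 in size. With baseline × time added, the error was at most about 0.003 in every scenario.

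**Step 4: direction.** Those scenarios lose low-baseline participants from the intervention group, so the estimate falls. Reversing the direction reverses the sign. With correlations 0.7/0.5/0.65 and dropout related to baseline in the intervention group only, a separate large run gave 0.426 or 0.374 depending on direction, and 0.449 with opposite directions by arm. With the interaction the estimates were 0.398–0.402.

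**Step 5: trial size.** 1,500 simulated trials of 380 with correlations 0.7/0.5/0.7:

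| Dropout | Common slope, mean (SD) | With baseline × time, mean (SD) |
|---|---|---|
| Completely random, 30/30 % | 0.406 (0.1005) | 0.406 (0.0991) |
| Intervention group only | 0.359 (0.1050) | 0.406 (0.1028) |
| Opposite by arm | 0.327 (0.1025) | 0.399 (0.1023) |

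Against a standard error of about 0.10, a bias of 0.02–0.07 is 0.2–0.7 standard errors. If the same bias arose under the null, two-sided type I error would be Φ(−1.96 + 0.2) + Φ(−1.96 − 0.2) = 5.5 % at the lower end and, with 0.7 in place of 0.2, 10.8 % at the upper.

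**The case against.** The strongest reply is that the shared slope is inferred from a term that a condensed article does not list. The text does not exclude baseline × time, and the registered SAP may contain it. This stands as a limit on the claim, but it does not dispose of the point. The article specifies the model down to the degrees-of-freedom method and names the one interaction with time, so an analyst following it would fit a common slope.

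Second, the required conditions are not documented. This also stands. A reader might infer that any MAR dropout, or simply unequal attrition between the arms, biases the primary result. It does not: dropout must relate to baseline or T1 differently by arm, and the slopes must differ as well. The Limitations section speaks only of higher attrition, not of attrition by arm or by baseline. That baseline predicts a nearer visit more strongly is a common pattern, but here it is an assumption.

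Third, the complete-case ANCOVA at T2 imposes no slope shared across visits. If dropout depends only on baseline and the model is linear, it estimates the T2 contrast without this bias. That is true, but it is a sensitivity analysis and does not carry the confirmatory test. It also ignores T1, so it gives no protection when T1 drives dropout. Jump to Reference changes the assumption about missing data and is not a check on the slope. A gap between the primary and complete-case results could then come from the slope restriction and be misread as evidence about missing data.

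**Conclusion.** The point holds as a low-cost improvement to the stated model. No figure in the protocol is wrong. As listed, the primary MMRM shares one baseline slope across weeks 6 and 12. When slopes differ by visit and the relation of dropout to baseline or T1 differs by arm, the T2 contrast is biased under MAR by roughly 0.01–0.07 SD, against a true effect of 0.40. Values of 0.10 SD or more need extreme decay of the correlations or a very strong dropout relation. All sizes rest on assumed correlations and dropout mechanisms.

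The second condition is plausible here: participants know their allocation, and the arms have different reasons to stay, since one has the app from the start and the other receives it only after T2. The documents do not show that it will occur. A reader might also infer that the restriction favours the app, or that it is conservative. Neither is supported, because the sign depends on who leaves which arm.

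**What to change.** First check the registered SAP. If baseline × time is already in the primary model, say so in the article's model description. If not, add it to the MMRM for the primary and all secondary outcomes before the data are analysed, and state that the test is the model-based group difference at T2.

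With two post-baseline visits the cost is one degree of freedom per outcome. No new data are needed and the sample size of 380 is unchanged. Precision is not visibly affected: under completely random dropout with correlations 0.7/0.6/0.75, the SD of the estimate was 0.0936 with the term and 0.0941 without it. Across the other simulated scenarios the two differed by about 2 % at most, in either direction, which is near the simulation error of an SD from 1,500 trials (1/√3000 = 1.8 %).
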